**Feasibility outcomes**				
Eligibility	T-0	Reception nurses, at the clinic, face to face	Eligibility screening checklist	Descriptive statistics
Intervention delivery	T-4	Primary researcher, at clinic facilities, researcher logbook review	Feasibility indexes include intervention fidelity, retention rate, and missing data rate	Descriptive statistics
**Acceptability outcomes**				
Acceptability	T-3	Primary researcher; at clinic facilities, telephone-interview	Self-design questionnaire including closed-ended and open-ended questions	**Quantitative data** Descriptive statistics Chi Square test comparing differences between groups of categorical variables **Qualitative data** A deductive approach of content analysis
**Effectiveness outcomes**				
Depression	T-0, -1, -2, -3	Primary researcher (T0, 3) and nurse coordinator (T-1, -2); at clinic facilities; face to face (T-0, -1, -2) and by telephone (T-3)	SMD-A	Descriptive statistics *t*-test/Mann–Whitney U test comparing baseline to T-3 *t*-test/Mann–Whitney U test comparing differences between groups at T-3 Linear regression measuring change over time
Perceived support	T-0, -1, -2, -3	As above	MOS-SSS	As above
Intimate relationship	T-0, -1, -2, -3	As above	CSI-4	As above
Coping behaviours	T-0, -2, -3	As above	CBCI	Descriptive statistics *t*-test/Mann–Whitney U test comparing baseline to T-3 of each coping style *t*-test/Mann–Whitney U test comparing differences between groups of each coping style at T-2 and T-3
Self-efficacy	T-0, -2, -3	As above	GSE-10	Descriptive statistics *t*-test/Mann–Whitney U test comparing baseline to T-3 *t*-test/Mann–Whitney U test comparing differences between groups at T-2 and T-3
Post-abortion growth	T-2, -3	As above	PTGI-SF	Descriptive statistics *t*-test/Mann–Whitney U test comparing T-2 to T-3 *t*-test/Mann–Whitney U test comparing differences between groups at T-2 and T-3
Abortion outcomes	T-3	As above	Self-design questions	Descriptive statistics Chi Square test comparing differences between groups at T-3

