##### Abortion Related Outcomes

Abortion related outcomes will be measured according to women’s gestational weeks at abortion, type of abortion, complications, and follow-up-exam attendance.

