### 2.5. Sample Size

A formal sample-size calculation is not necessary for research objectives 1 and 2 [20]. For objective 3, G*Power software was used to determine reasonable sample size for the estimation of differences between intervention and control groups. The effect size on depression reported by similar interventions ranged from 0.39 to 1.06 [37,38,39]. G*power indicated a total of 72 participants will be required to detect a 0.39 effect size for depression, two tailed, with alpha at 0.05 and power at 90%. Anticipating a 20% attrition rate, recruitment was set at 90 (45 women per group).

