**Figure 2 ijerph-19-06611-f002:**
[figure not shown]
SPIRIT standard flow diagram.

**Table 1 ijerph-19-06611-t001:** Intervention description according to TIDieR checklist.

TIDieR Item	Intervention Group	Control Group
**1.** **BRIEF NAME**	The START intervention	Standard abortion care
**2.** **WHY**	Based on the Transactional Model of Stress and Coping, the START intervention intends to help women cope with abortion experience by addressing the specific stressors they face in the Chinese context, hence promoting well-being	N/A
**3.** **WHAT-Materials**	Consultation, an information booklet, a WeChat-based public profile page, and a hotline	N/A
**4.** **WHAT-Procedure**	All participants allocated to the intervention group will be offered a 30-min face-to-face consultation. The consultation includes a brief introduction of the public profile page, Q&A, and offering emotional support and information on available coping resources. A printed information booklet will be provided during the consultation. Meanwhile, by scan the QR code, participants will be endowed with unlimited access to the public profile page till the closure of the project. A hotline will also be offered.	(1) prior abortion consultation on informed choice of pregnancy; (2) abortion preparation education on abortion practice, and steps involved; (3) a brief discharge education session on warning signs of potential complications and post-abortion contraception; and (4) a regular 2-week post-abortion appointment to determine the completion of the abortion.
**5.** **WHO PROVIDED**	The consultation, information booklet, and managing the public profile page will be carry out by the primary researcher who is a qualified abortion counsellor. Hotline will be answered by a registered nurse who has more than 10 years clinical experience in abortion care.	Prior abortion consultation and post-abortion exam-by doctors Abortion preparation and discharge education-by nurses
**6.** **HOW**	Consultation (face to face) Information booklet (hard copy) Public profile page (internet) Hotline (telephone)	Face to face
**7.** **WHERE**	Consultation (the consultation room) Information booklet (the consultation room) Public profile page (WeChat based) Hotline (telephone-base)	Health centre facilities

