**8.** **WHEN and HOW MUCH**	Consultation (after women made their abortion appointment, 30 min) Information booklet (during the consultation, one copy to take home) Public profile page (from the consultation, unlimited access until the closure of the project) Hotline (from the consultation, available during workhours)	Prior abortion consultation—at women’s first appointment (10–20 min); Abortion preparation education—after women made their abortion appointment (5–10 min); post-abortion education—before women are discharged (10 min); The post-abortion exam—2 weeks after abortion
**9.** **TAILORING**	Participants in the intervention group will receive the same intervention	N/A
**10.** **MODIFI-CATION**	Cannot be reported until the study is complete	N/A
**11.** **HOW WELL**	The research nurse and reception nurses involved in the trial will be trained initially. A researcher logbook will be kept recording intervention delivery of each participant. Adherence to the intervention will be assessed by participants self-reported usage info collected during follow-ups	N/A
**12.** **ACTUAL**	Cannot be reported until the study is complete	N/A

Abbreviations: Q&A: questions and answers; N/A: not applicable.

**Table 2 ijerph-19-06611-t002:** Content of the information booklet and platform.

Categories	Themes	Example Items
Abortion	Facts about abortion	General information about abortion Pregnancy calculation and ectopic pregnancy Abortion practice in Beijing
	Different types of abortion	Medical abortion and steps involved Aspiration/surgical abortion and steps involved Features of aspiration abortion and medical abortion
	Q&A	What is your legal position, e.g., gestation age limits; no need for husbands’ or partners’ permission; and Nation ID required etc. How much does abortion cost? Does abortion hurt and what is a painless induced abortion? What will you experience during an abortion? How could you know your abortion is complete? Will an abortion cause infertility? How will you feel if you have an abortion
	Aftercare and follow-up examination	Follow-up examination and why it is necessary Symptoms requiring contacting your health provider, going to local emergency room, or calling 120 for Emergency Health Aid.
Intimate Relationship	A healthy relationship	Important characteristics of a healthy relationship Rights and responsibilities in a relationship Equality in intimate relationships

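### Complications and the other abortion-related outcomes are scheduled only at the six-week telephone call, although study staff already meet the women on the abortion day and at the two-week exam visit

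*Protocol article*

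**What the plan says.** Section 2.4.3 (Abortion Related Outcomes) lists four items: "gestational weeks at abortion, type of abortion, complications, and follow-up-exam attendance". In Table 3, the abortion-outcomes row gives T-3 as the only time, self-designed questions as the measure, and "Chi Square test comparing differences between groups at T-3" as the between-group analysis. Its method column refers back to the depression row, which names the collectors as "Primary researcher (T0, 3) and nurse coordinator (T-1, -2" and the mode as "face to face (T-0, -1, -2) and by telephone (T-3". At T-3 this means the primary researcher, by telephone, at six weeks (section 2.8).

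Section 2.8 places T-1 on the abortion day before discharge, and T-2 at the post-abortion exam visit, normally two weeks after the abortion. Table 3 has the nurse coordinator collecting other outcomes on both occasions. Section 2.7 says that participants, providers and data collectors cannot be blinded. Table 1 (item 5) says the primary researcher delivers the START consultation.

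**The concern.** Complications are the only physical-safety outcome listed in the article. Collecting them once, at the last contact, ties the safety data to retention: a woman who drops out after T-1 or T-2 has been seen by study staff but was never scheduled to be asked. If a complication makes a woman more or less likely to answer at six weeks, the loss is not random.

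Reporting may also differ by arm. Only START women receive the booklet and online platform, which include "Symptoms requiring contacting your health provider, going to local emergency room", together with a hotline and a WeChat page until six weeks. They may recognise or mention more events. The caller knows the allocation and delivered the intervention.

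The other items lose as well. Type of abortion and gestation are settled by the abortion day, so asking six weeks later adds recall error for no gain. Attendance known only for T-3 responders would be biased upward if women who skip the exam are also the ones who do not answer the call.

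**Working it through.** **Plan's own figures.** Section 2.5 needs 72 evaluable women and states: "Anticipating a 20% attrition rate, recruitment was set at 90 (45 women per group". Check: 72 / (1 − 0.20) = 90, which reproduces. Section 2.10 moves to 110 at 35% attrition: 72 / (1 − 0.35) = 110.8, so 111 against the stated 110, which is close enough. Whether 72 is itself right is a separate question that does not affect this point.

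**Women with no scheduled complication data** (attrition × N):
- 0.20 × 90 = 18
- 0.35 × 110 = 38.5, about 38

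**Expected complications missed.** The documents give no complication rate. Assume 2%, 5% or 10%, with drop-out unrelated to complications (attrition × N × risk):
- N = 90, 20% lost: 0.4, 0.9 or 1.8 missed, out of 1.8, 4.5 or 9.0 expected
- N = 110, 35% lost: 0.8, 1.9 or 3.9 missed, out of 2.2, 5.5 or 11.0 expected

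**Bounds with no assumption about the women lost.** If 10% of those retained report a complication, the proportion among all randomised women lies between retained × 0.10 and that value plus the fraction lost:
- 20% lost: 0.80 × 0.10 = 8%, up to 8% + 20% = 28%
- 35% lost: 0.65 × 0.10 = 6.5%, up to 6.5% + 35% = 41.5%

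**Precision if no event is seen.** One-sided 95% upper limit, 1 − 0.05^(1/n):
- n = 36 per arm (45 × 0.80): 8.0%
- n = 45 per arm: 6.4%

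The second figure assumes that every woman's data are recovered, so the gap is the most that better collection could gain.

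**Differential reporting (assumed rates).** With equal true risk, and 90% of complications reported in one arm against 60% in the other, the apparent risk ratio is 0.90 / 0.60 = 1.5 with no real difference.

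**Attendance (assumed pattern).** If the 18 women lost and 9 others skipped the exam, T-3 responders show 63/72 = 87.5%, against 63/90 = 70% of all randomised women.

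**When each item could first be known:**
- Gestational weeks at abortion: by T-1. Current gestation is already taken at T-0 under participant characteristics.
- Type of abortion: by T-1.
- Complications: immediate ones at T-1, those up to two weeks at T-2, later ones at T-3.
- Exam attendance: T-2, since that contact takes place at the exam visit.

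**The case against.** Much can be said for the plan. A single question at six weeks covers the whole follow-up window, including events after the exam. Put to every woman in the same words, it does not depend on who attended. Current gestation is already recorded at T-0, and attendance can largely be inferred from completion of T-2, so only complications and type of abortion are fully exposed. Both arms receive the standard discharge education on warning signs, because START is added to standard care. This is also a feasibility and preliminary-efficacy trial, and no primary or feasibility conclusion rests on this row. Source-document detail may sit in a fuller protocol that is not shown.

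These points limit the size of the concern. They do not remove it. Section 2.8 presents Table 3 as the detailed account of who collects what, when and how. Where that table relies on a log review, as it does for intervention delivery, it says so; the abortion-outcomes row names no such source. A T-3 question can be kept and earlier ones added.

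A reader might infer more than the text supports:
- That completion of the abortion is also collected only once. It is not a listed outcome. It appears only as the purpose of the standard-care visit, "a regular 2-week post-abortion appointment to determine the completion of the abortion".
- That doctors establish complications at that exam. The stated purpose is completion only, and later events could not be seen there.
- That the centre holds complication data on nearly every woman. The article does not say so. Section 2.10 foresees excess drop-out at the two-week follow-up itself, and a woman lost there may have no exam record.
- That the comparison should rest on the clinic record alone. The START material explains why the follow-up exam is necessary (Table 2). If START raises attendance, record-based detection would be higher in that arm.

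**Conclusion.** The point holds as a cheap improvement to a stated schedule. On the text, a woman lost before T-3 has no scheduled data on complications or type of abortion, although study staff may have met her at T-1 and T-2. The size is up to 18 of 90 women at 20% attrition and about 38 of 110 at 35%. These are ceilings on what earlier collection could recover, because some women will be lost before T-2 and some events will come later.

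Arm-dependent reporting is a risk created by unblinded women, an unblinded caller who delivered START, and extra contact in one arm. The documents do not show that it happens, and the 1.5 ratio rests on assumed reporting rates. The complication risks are likewise assumed. That T-3 is self-report without records is a reasonable inference from the telephone mode and the self-designed questions, not an explicit statement.

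**What to change.** In Table 3, change the time of the abortion-outcomes row from T-3 to T-1, T-2 and T-3, and state the source of each item:
- T-1: gestational weeks at abortion, type of abortion, immediate complications.
- T-2: complications to date.
- Exam attendance: from the clinic's visit log for every randomised woman, whether or not she answers at T-3.
- T-3: the same fixed questions in both arms about events since the last contact and care received elsewhere.

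Compare complications between arms using all sources combined, and report them by source (T-1/T-2 or clinic record, and T-3 self-report). Do not rely on the exam record alone, because attendance may differ by arm.

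The cost is a few extra items at visits that already exist, some staff time, and consent wording if clinic records are used. Events after two weeks and care received elsewhere will still rest on self-report.

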## Abstract

Background: Although undergoing an abortion is stressful for most women, little attention has been given to their psychological wellbeing. This protocol aims to assess the feasibility, acceptability, and primary effects of a complex intervention to promote positive coping behaviors and alleviate depression symptoms among Chinese women who have undergone an abortion. Methods: A two-arm randomized controlled trial design will be used. Participants will be recruited at their first appointment with the abortion clinic and randomly allocated to receive either the Stress-And-Coping suppoRT (START) intervention (in addition to standard abortion care) or standard care only. All participants will be followed-up at two- and six-weeks post-abortion. Approval has been granted by local and university ethics committees. This research was supported by an Australian Government Research Training Program Scholarship. Discussion: The results will assist refinement and further evaluations of the START intervention, contribute to improved abortion care practices in China, and enrich the evidence on improving women’s psychological well-being following abortion in China. Trial registration: Registered at the Chinese Clinical Trials.gov: ChiCTR2100046101. Date of registration: 4 May 2021.

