Abortion occurs in a socio-cultural context, and local policies regarding abortion accessibility play an important role in women’s psychological response toward an abortion. As the most populous country in the world, about 10 million abortions were conducted in China in 2019 [15]. China has one of the most liberal abortion policies amongst Asian countries, which allows first-trimester abortion without restriction, except for the prohibition of sex-selective abortions. Abortion is also socially acceptable in China, and most abortions that occur in China are due to unwanted pregnancies consistent with a societal desire for small families and timed birth. A recent study revealed that around a quarter of women seeking an abortion in China experienced high stress and moderate-to-severe depression [16]. Chinese women’s unmet support needs when seeking abortion were predictive of adverse psychological outcomes.

In the absence of available evidence, our research team developed the STress-And-coping suppoRT intervention (START). Underpinned by the Transactional Model of Stress and Coping, the START intervention will provide women with information, coping skills, and support to achieve positive short- and long-term health. The intervention is innovative and based on (1) current available evidence, (2) a sound understanding of the target population, (3) informed by Medical Research Council (MRC) guidance for complex interventions [17], (4) the Intervention Mapping (IM) framework [18], and (5) a five-step iterative pathway to gradually shape the intervention design [19].

The aim of this trail is to assess the START intervention among Chinese women undergoing an abortion. Its specific objectives are to:Determine the feasibility of the START intervention according to eligibility, recruitment, intervention delivery, and retention data;Evaluate the acceptability of the START intervention among participants based on the Theoretical Framework of Acceptability (TFA) of Health Care Interventions;Test the preliminary efficacy of the START intervention on women’s depression symptoms, coping behaviors, self-efficacy, perceived support levels, intimate relationship satisfaction, post-abortion personal growth, and abortion relevant outcomes compared with women receiving standard abortion care.

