### 2.8. Data Collection

Data collection will occur at five timeframes: T-0, during recruitment before randomization; T-1, on abortion day before discharge (normally 2 h post-abortion procedure); T-2, during women’s post-abortion exam visit, normally 2 weeks post-abortion; T-3, 6 weeks post-abortion; and T-4, post completion of all follow-ups of all participants. See Table 3 for detailed information on data collection, including What, Who, When, Where, How, and by What data.

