Limitations, however, need to be considered. The emotional period between a woman’s initial appointment with the clinic and 6 weeks post-abortion [46], as well as the sensitive nature of the topic, could challenge women’s adherence and completion of the study. Strategies such as keeping information simple, offering the intervention in confidential formats, and repeated reminders that are known to be effective in improving intervention adherence will be employed [47]. Another challenge lies in the uncertainties of the COVID-19 pandemic. We will follow and document all local, national, and international measures that may impact our study progress. The actual delivery of the intervention and identified barriers and facilitators of implementing the intervention will be well-recorded to inform future studies.

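### Table 3 lists baseline-to-T-3 tests as effectiveness analyses without calling them descriptive, although a within-arm change cannot answer the comparative objective 3

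*Protocol article*

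**What the plan says.** Objective 3, at the end of the Introduction, is comparative. It closes its list of outcomes with "abortion relevant outcomes compared with women receiving standard abortion care". Section 2.5 likewise sizes the trial for a difference between the two arms.

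The effectiveness rows of Table 3 give these analyses:

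- **Depression (primary), perceived support, intimate relationship:** descriptive statistics; a t-test or "Mann–Whitney U test comparing baseline to T-3"; a t-test or Mann–Whitney "U test comparing differences between groups at T-3"; and "Linear regression measuring change over time".
- **Coping and self-efficacy:** descriptive statistics, a baseline-to-T-3 test, and between-group tests at T-2 and T-3.
- **Post-abortion growth:** the same pattern, but the before-after test runs from T-2 to T-3 because growth is not measured at T-0.
- **Abortion outcomes:** a between-group chi-square test at T-3 only. The point does not apply here.

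Section 2.8 fixes the baseline as "T-0, during recruitment before randomization", which is before the abortion, and puts T-3 at six weeks after it. Neither Table 3 nor section 2.9 says that the before-after tests are descriptive or that they rank below the between-group tests.

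**The concern.** A before-after test within one arm estimates the effect of START plus everything else that happens between booking an abortion and six weeks after it. It does not use the randomised comparison. If scores move in both arms for reasons unrelated to START, the test treats that movement as improvement. Pairing the observations correctly does not help, because a correct paired test answers the same non-comparative question.

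Table 3 has a separate entry for descriptive statistics, so the before-after tests are evidently meant as inference. A p-value for change in the START arm would then sit in the effectiveness results beside the between-group p-value, with nothing in the article to say which of them bears on preliminary efficacy. According to the Conclusions, the results are meant to shape the intervention and lead to a larger trial.

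**Working it through.** **Inputs from the protocol article.** Section 2.5 recruits 90 women (45 per arm) and allows for 20% attrition: 90 × (1 − 0.20) = 72 completers, or 36 per arm. This reproduces the step from 72 to 90. The figure of 72 is used here only as the number of completers. Whether it suits a between-group effect of 0.39 is a separate question. Tests are two-sided at 5%.

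**Inputs assumed, because the documents give none.** START has no effect. Mean scores fall by g standard deviations from T-0 to T-3 in both arms alike, with g from 0 to 0.8. The correlation ρ between a woman's T-0 and T-3 scores is 0.3, 0.5 or 0.7. Each within-arm test is a correct paired t-test.

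**Formula.** The standardised mean change is dz = g / √(2(1 − ρ)). The paired t statistic on n = 36 has 35 degrees of freedom and noncentrality dz × √36 = 6·dz. The probability of significance is the probability that it lies beyond the two-sided 5% limits.

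- g = 0.2, ρ = 0.3: dz = 0.2/√1.4 = 0.169; noncentrality 1.01; probability 0.167.
- g = 0.2, ρ = 0.7: dz = 0.2/√0.6 = 0.258; noncentrality 1.55; probability 0.325.
- g = 0.5, ρ = 0.3: dz = 0.5/√1.4 = 0.423; noncentrality 2.54; probability 0.693.
- g = 0.5, ρ = 0.7: dz = 0.5/√0.6 = 0.645; noncentrality 3.87; probability 0.964.

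Probability that the START arm shows a significant change when START does nothing:

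| Common fall g (SD) | ρ = 0.3 | ρ = 0.5 | ρ = 0.7 | Between-group test at T-3 |
|---|---|---|---|---|
| 0 | 0.050 | 0.050 | 0.050 | 0.05 |
| 0.2 | 0.167 | 0.215 | 0.325 | 0.05 |
| 0.3 | 0.316 | 0.417 | 0.618 | 0.05 |
| 0.5 | 0.693 | 0.831 | 0.964 | 0.05 |
| 0.8 | 0.976 | 0.997 | 1.000 | 0.05 |

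The last column comes from simulation with 20,000 runs per setting, which gave 0.051 throughout. A shift common to both arms cancels from the difference between them, so the between-group test keeps its nominal level whatever g is.

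**Sensitivity to the test used.** The t-test and Mann–Whitney pair named in Table 3 is an independent-samples pair if taken literally. An unpaired t-test applied to the same women's two measurements is significant in 0.03–0.09 of simulated trials at g = 0.2 and 0.56–0.59 at g = 0.5 over the same correlations. The inflation is then smaller for a small fall but still large at half a standard deviation.

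**The case against.** The strongest reply is that the valid comparison is already there. The same cells of Table 3 list between-group tests, section 2.9 speaks of detecting differences between groups, and the Discussion promises adjustment for baseline differences. This stands. A reader might infer that START will be declared effective on a before-after p-value, or by noting which arm reached significance. No passage adopts either rule, and appearing first in a table cell does not give a test priority.

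A reader might also infer that the documents predict natural recovery by six weeks. They do not. The Introduction's statement that "around a quarter of women seeking an abortion in China experienced high stress and moderate-to-severe depression" is a prevalence and gives no course over time. The Discussion sentence containing "The emotional period between" concerns adherence and completion, and the period it describes includes the six-week visit. The Introduction also says that distress persists in some women. Natural change is plausible, but its size, and even its presence for support, relationship satisfaction or self-efficacy, is not documented. This is why the calculation starts from zero change.

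The within-arm reading is itself an inference, since Table 3 does not say that the test is done within each arm. The entry could mean a between-arm comparison of change, in which case only the wording needs correcting. The separate between-group line that follows makes this less likely. A before-after test pooled over both arms would not be comparative either.

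Finally, this is a feasibility and preliminary-efficacy trial, and describing change in each arm is reasonable. That supports showing the changes, not testing them as effectiveness results. Ranking of tests may be left to an analysis plan, but here the article itself lists the before-after test among the effectiveness analyses.

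**Conclusion.** The point holds as one of labelling and interpretation. Read as within-arm tests, the baseline-to-T-3 tests (T-2 to T-3 for growth) do not address START compared with standard care, yet they stand unmarked beside the tests that do. With no START effect and 36 completers per arm, the chance of a significant START-arm change runs from 0.05 with no common change to 0.17–0.33 at a 0.2 SD fall and 0.69–0.96 at a 0.5 SD fall. The between-group test stays at 5%. These figures rest on an assumed common change, correlations of 0.3–0.7 and a correct paired test. The direction does not depend on the particular values: under these assumptions any non-zero common change takes the within-arm rate above 5%. The calculation uses the T-0 to T-3 interval. For growth the same logic applies from T-2 to T-3, without the argument from a pre-abortion baseline. The planned between-group comparison is neither missing nor replaced.

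**What to change.** In Table 3, replace the baseline-to-T-3 tests, and the T-2-to-T-3 test for growth, with descriptive within-arm summaries: means and mean changes with 95% confidence intervals and no p-values.

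Add one sentence to section 2.9 saying that preliminary efficacy is judged on between-arm contrasts. The main contrast would be the T-3 difference with its 95% confidence interval, preferably adjusted for the baseline score where one is collected (growth has none). Keep the planned between-group comparisons at T-2 for coping, self-efficacy and growth. Keep the regression over time for depression, support and relationship, and state that it includes a group-by-time term.

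If the authors in fact meant a between-arm comparison of change, they should say so in Table 3.

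The cost is a few lines of wording. No new data or visits are needed, and the only loss is the within-arm p-values.

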#### 2.4.3. Effectiveness Outcomes

Effectiveness outcomes include women’s depression symptoms (primary), coping behaviours, self-efficacy, perceived support levels, intimate relationship satisfaction, post-abortion personal growth, and abortion-relevant outcomes. Specific measures include:

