### 2.10. Protocol Modifications

During the conduction of the trial, if we observe a higher-than-expected drop-out rate at the two-weeks post-abortion follow-up, we will increase the sample size from 90 (calculated on a 20% attrition rate) to 110 (calculated on a 35% attrition rate) to achieve precision for the estimation of the effect size. Paper-based questionnaires will be left for women to fill out on their own. However, if participants express being overwhelmed by the amount of information required, we will conduct an interview during which participants could ask clarifying questions. This approach will minimize missing data and enhance the retention rate.

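### The between-group depression test uses T-3 scores alone and so discards the earlier scores of women not reached at six weeks; the listed regression over all visits should carry the comparison

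*Protocol article*

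**What the plan says.** Section 2.4.3 of the protocol article ranks the outcomes: "Effectiveness outcomes include women’s depression symptoms (primary"). The third objective in the Introduction is to "Test the preliminary efficacy of the START intervention on women’s depression symptoms" and other outcomes, against standard abortion care.

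Table 3 (Effectiveness outcomes, Depression row) schedules the measure at T-0, T-1, T-2 and T-3, collected "face to face (T-0, -1, -2) and by telephone (T-3"). Section 2.8 defines the last of these as "T-3, 6 weeks post-abortion". The analysis cell lists descriptive statistics, a baseline-to-T-3 comparison, and then two items that run together in the text: a t-test or Mann-Whitney U test "comparing differences between groups at T-3 Linear regression measuring change over time". The arm comparison belongs to the T-3 test. The regression is described only as a measure of change over time, and section 2.9 adds only that it is a general linear regression.

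On attrition, section 2.5 says: "Anticipating a 20% attrition rate, recruitment was set at 90 (45 women per group"). Section 2.9 sets a retention criterion of less than 20% lost at six weeks. Section 2.10 adds a contingency, triggered by higher-than-expected drop-out at two weeks: "we will increase the sample size from 90 (calculated on a 20% attrition rate) to 110 (calculated on a 35% attrition rate"). The limitations in the Discussion say that the emotional nature of the weeks up to follow-up and the sensitivity of the topic "could challenge women’s adherence and completion of the study".

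**The concern.** A two-sample test at one visit can use only women who have a score at that visit. A woman assessed at T-0, T-1 and T-2 but not reached by telephone at week 6 contributes nothing to the only stated between-arm comparison of depression. Her earlier scores, already collected, say something about what her T-3 score would have been.

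If the chance of being lost is related to depression, the women left at T-3 are a selected group. Recruiting more women, as section 2.10 allows, restores the number of scores but not the balance of who provides them. Loss could also act differently by arm. Only START women have the consultation, the hotline and the WeChat channel (section 2.3), and neither participants nor data collectors are blinded (section 2.7). The results are meant to direct a later full-powered trial (section 4), so a distorted difference would be carried forward.

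**Working it through.** **Inputs from the protocol article.** Effect size 0.39, 72 women required, 20% attrition and a target of 90 (section 2.5); 35% attrition and a target of 110 (section 2.10); 1:1 allocation (section 2); depression at T-0 to T-3 (Table 3). The 72 is taken as stated.

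**Step 1: the plan's own figures.** Target = N / (1 − loss).
- 72 / (1 − 0.20) = 90, as stated; 90 × 0.20 = 18 women without T-3.
- 72 / (1 − 0.35) = 110.8, against the stated 110; 110 × 0.35 = 38.5, so about 38 women without T-3.

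In both cases the T-3 test is expected to rest on about 72 women.

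**Step 2: when the T-3 difference is biased.** Let p be the proportion lost in an arm and g the mean T-3 score of lost women minus that of retained women. An arm's full mean is its retained mean plus p × g. The retained women's difference (control minus START) therefore falls short of the full difference by

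p(control) × g(control) − p(START) × g(START).

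- Equal p and g in both arms: no bias, even though both arm means are too low.
- Illustration with 25% lost in control, 15% in START and g = 0.5 SD: 0.25 × 0.5 − 0.15 × 0.5 = 0.05 SD, or 0.05 / 0.39 = 13% understatement.
- The same rates swapped: 13% overstatement.

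**Step 3: size under assumed drop-out models.** The article gives no drop-out model, so these are assumptions: four standardised scores with correlation 0.5 to 0.7 between visits, a true effect of 0.39 SD at T-2 and T-3, and logistic loss before T-3 depending on the T-2 score. Slopes are log-odds per SD. The figures are mean differences, so they apply to the t-test.

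| Mechanism | T-3 difference, 20% loss | T-3 difference, 35% loss |
|---|---|---|
| Loss unrelated to depression | 0.39 | 0.39 |
| Equal loss rate and equal dependence within each arm | 0.39 | 0.39 |
| One common function of score in both arms, slope 0.5 to 1.5 | 0.34 to 0.38 | 0.32 to 0.38 |
| Distress-related loss in controls only, slope 0.7 to 1.0 | 0.26 to 0.32 | 0.18 to 0.28 |

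With one mechanism in both arms, the largest bias is (0.39 − 0.32) / 0.39 = 18%. With controls only, the extreme is (0.39 − 0.18) / 0.39 = 54% understatement. Distress-related loss in START only (slope 0.7) gave 0.45 to 0.54 over the two loss rates, that is (0.45 − 0.39) / 0.39 = 15% to (0.54 − 0.39) / 0.39 = 38% overstatement. In the controls-only case the arms' loss rates differed by only about 1.5 to 4 percentage points, so similar retention by arm would not rule the problem out.

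**Step 4: what using the earlier scores recovers.** T-3 was regressed on T-0 to T-2 within each arm and predicted for all randomised women. This relies on the same missing-at-random assumption as a mixed model.
- Loss depending on the observed T-2 score: 0.38 to 0.40 in every scenario.
- Loss depending on the unseen T-3 score, controls only: 0.19 to 0.33, against 0.08 to 0.26 for the T-3 test. This was better in every case but not a cure.

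**The case against.** **Missing-data handling is normally left to the SAP or full protocol, neither of which is shown.** This stands as far as it goes. The article defines no analysis set and does not rule out imputation, and that silence is no finding. The point rests on what Table 3 does fix: a single-visit test as the arm comparison.

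**The same cell lists a regression over the repeated scores.** This also stands in part. The T-3 test is not the only analysis, and the regression could retain women lost before T-3. As described, however, it states no arm-by-visit contrast and no within-woman correlation. The Discussion's remark about adjusting for baseline differences does not appear among the Table 3 tests.

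**The bias may be small beside the noise.** With 36 women per arm, the 95% CI half-width is about 1.96 × √(2/36) = 0.46 SD, against a bias of at most about 0.07 SD (0.39 − 0.32) when one mechanism acts in both arms. This is fair and limits the urgency. The larger figures need a mechanism that differs by arm, which is plausible but nowhere stated.

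**Readings that go too far.** A reader might infer that the plan expects 20% to 35% loss. It expects 20%, and 35% is a contingency. A reader might also take the limitations to say that more depressed women will leave. They name an emotional period and a sensitive topic, which apply to all participants, alongside measures to support adherence. Informative loss is a reasonable inference and not a documented fact.

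**Conclusion.** The point holds as a cheap improvement. As written, the arm comparison for the primary effectiveness outcome discards the T-0 to T-2 scores of women without a T-3 score, about 18 of 90 at the planned loss.

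The size is conditional. It rests on a true effect of 0.39 SD, the assumed correlations and slopes, and loss that depends on the T-2 score. On that basis the bias is about 0 to 18% with one mechanism in both arms, and larger in either direction if the mechanism differs by arm. It is zero if loss is unrelated to depression.

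Two stronger conclusions are not supported. One is that a true START effect will be understated: the article does not fix the direction, and reversing the arm affected gave an overstatement. The other is that an all-scores analysis removes the problem: it does so only if loss depends on observed scores.

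**What to change.** In section 2.9 and the Depression row of Table 3:

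- Turn the listed regression into the main efficacy analysis: a linear mixed model (available in SPSS) on all randomised women by allocated arm, with every available score from T-0 to T-3, terms for visit and arm-by-visit, and within-woman correlation. Report the arm difference at T-3 with its 95% CI.
- Keep the T-3 t-test or Mann-Whitney U test as a sensitivity analysis.
- Add a sensitivity analysis that shifts the missing T-3 scores towards worse depression, separately by arm, for example by 0 to 0.5 SD.

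The cost is a change of wording and a little more analysis work, with no new data, visits or participants. The downside is that the model assumes missing at random given the observed scores. If loss depends on the unseen T-3 score, it reduces the bias without removing it, which is why the shift analysis is needed.
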